#### Anthropometric measures

Body weight will be measured using a digital scale in the CU-AMC Anschutz Health and Wellness Center clinic accurate to ±0.1 kg at baseline and at weeks 13, 26, 39, 52, and 78 in the AM, after an overnight fast. Participants will also be given a smart scale (©BodyTrace smart scales (Palo Alto, CA)) for daily home weighing use during the 52-week study intervention. These daily weights will be transmitted via wireless cellular network to a secure website. Height will be measured to the nearest 1 mm with a stadiometer at baseline. Blood pressure will be measured with a manual sphygmomanometer (average of 2 seated values taken after 5 min rest) at baseline and weeks 13, 26, 52, and 78. Waist circumference (cm) will be measured at baseline and weeks 13, 26, 52, and 78 with a tape measure parallel to the floor, just superior to the iliac crest. Fat mass and lean mass will be measured using dual-energy x-ray absorptiometry (DXA) at baseline and weeks 26, 52, and 78.

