#### Strategies to improve adherence to interventions {11c}

#### Group-based behavioral support

To improve adherence to the interventions, both groups will receive a 52-week group-based behavioral weight loss program with equivalent contact and support (see Table 2 for a list of weekly behavioral support topics). The programs will fulfill all recommendations for behavioral interventions for treatment of obesity outlined in current guidelines [17]. Randomized groups will meet separately. Curriculum for DCR will be based on the Colorado Weigh behavioral weight loss program which was developed at CU-AMC in 2000 and uses a skills-based approach and cognitive behavioral strategies for lifestyle modification with a dietary focus on DCR [44, 45]. Curriculum for IMF will also be based on the Colorado Weigh behavioral weight loss program and features similar weekly curriculum themes as used in DCR but adapted by the study PI (VC) with input from a registered dietitian (KB) and a behavioral psychologist (AC) to focus on behavioral support specific to IMF. Group meetings will be taught by a registered dietitian with experience in leading group-based behavioral weight loss interventions. Groups will meet weekly during weeks 0–13 and every 2 weeks during weeks 14–52. Weight will be obtained at each group meeting. Group sessions will last ~60 min and the curriculum will be delivered using a mix of large group discussion, small breakout discussions, visual demonstrations, and written exercises. Participants in the IMF group will be instructed in specific strategies to support IMF including strategies to deal with hunger on fast days, distraction techniques, and choosing a balanced diet/appropriate portions on fed days. Participants in the DCR group will be instructed in specific strategies to support DCR with a focus on daily calorie counting and food logging. Topics covered in both groups during the first 26 weeks include realistic weight loss goal setting, self-monitoring strategies, mindful eating, stress management, cognitive restructuring, improving personal food environments and social networks, and strategies to overcome barriers to healthy eating and increasing PA. Later in the curriculum (weeks 27–52), topics will focus on strategies for weight loss maintenance and include impact of weight loss on EE and propensity for weight regain, relapse prevention, and identifying motivation for long-term dietary and PA changes. Participants will also be provided two 10–15 min 1:1 phone calls with their group leader during the initial 26 weeks of the intervention for individualized dietary goal setting using a standardized protocol.

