### Outcomes {12}

Participants will be asked to complete assessment visits at baseline and weeks 13, 26, 39, and 52 during the intervention as well as a follow-up assessment 26 weeks after completion of the 52-week study intervention (i.e., at week 78). See Table 3 for assessments by study timepoint. Body weight, measured in the clinic, is the primary study outcome. Among participants allocated to IMF, outcomes will be measured after a fed day.

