**Table 3 Tab3:**
[figure not shown]
Schedule of enrollment, interventions, and assessments for the DRIFT study participants

*EI* energy intake, *REE* resting energy expenditure, *TDEE* total daily energy expenditure, *PAEE* physical activity energy expenditure, *PAL* physical activity level, *MVPA* moderate-to-vigorous physical activity

*All measures, post-allocation, will occur ±2 weeks from when the measure is due

**Screening measures include blood draw (complete blood count (CBC)), comprehensive metabolic panel (CMP), lipid profile, thyroid stimulating hormone (TSH), and hemoglobin A1C, electrocardiogram, height in centimeters (stadiometer), and physical exam and medical history

^#^Outcome weights will be taken in the morning, after an overnight fast, with the participant wearing a hospital gown. In the IMF group, weight will be taken in the morning following a fed day. Weight will also be measured weekly during weeks 0–26 and every other week during weeks 27–52 at the group-based behavioral weight loss sessions

^##^These measures will be collected monthly

^*†*^Outcome labs include glucose, insulin, triglycerides (TG), free fatty acids (FFA), beta-hydroxybutyrate (BHB), and cortisol. These will be measured at baseline after both a fed (i.e., 12-h fast) and fast day (i.e., 36-h fast, with exception of 25% EI). A lipid panel, insulin, glucose, hemoglobin A1C, leptin, ghrelin, peptide YY, highly sensitive C-reactive protein (hs-CRP), and brain-derived neurotrophic factor (BDNF) will be performed at baseline and weeks 26 and 52

^***††***^ Stored blood and stool samples will be collected at baseline and weeks 13, 26, 52, and 78 in subjects who consented to sample storage

^***†††***^See Table 4 for a detailed list of each construct for psychosocial, behavioral, and environmental factors

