#### Methods in analysis to handle protocol non-adherence and any statistical methods to handle missing data {20c}

The primary analysis will use the “intent-to-treat” principle to test our study hypotheses under practical and realistic conditions. All randomized participants will be analyzed. We expect that missingness condition is either missing completely at random (MCAR) or missing at random (MAR). A linear mixed effects model will serve as the primary method to handle missing values. The primary and secondary outcomes will be further examined using various sensitivity analyses including analysis of completers using the above statistical models; imputing missing values using baseline-observation-carried-forward, and then assessing efficacy by analyzing the change score from baseline using two sample *t*-tests or linear regression model while adjusting for other covariates; and finally imputing missing values using Markov chain Monte Carlo multiple imputation to create 20 imputed data sets and then analyzing the data using the linear mixed effects model.

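### The stated missing-data methods leave unused the class and home-scale weights collected up to week 52, and baseline carried forward can overwrite a recently observed weight with zero change

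*Protocol article*

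**What the plan says.** - **Primary measure.** Outcomes {12}: "Body weight, measured in the clinic, is the primary study outcome". Anthropometric measures gives the schedule: "at baseline and at weeks 13, 26, 39, 52, and 78 in the AM, after an overnight fast". The Table 3 footnote adds a hospital gown and, for one arm, a further condition: "In the IMF group, weight will be taken in the morning following a fed day".
- **Home weights.** Anthropometric measures: participants receive a smart scale "for daily home weighing use during the 52-week study intervention", and "These daily weights will be transmitted via wireless cellular network to a secure website".
- **Class weights.** Group-based behavioral support: "Weight will be obtained at each group meeting". Table 2 lists classes at weeks 40, 42, 44, 46, 48, 50 and 52.
- **Missing data {20c}.** "A linear mixed effects model will serve as the primary method to handle missing values", under MCAR or MAR. The sensitivity analyses named are completers, BOCF with a change-score comparison, and MCMC multiple imputation with 20 data sets.
- **Fallback.** Sample size {14}: if superiority of IMF is not shown, non-inferiority is tested with a margin of 2.26 kg.

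Neither Statistical methods {20a} nor {20c} gives home or class weights a role as outcome, substitute value or auxiliary variable.

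**The concern.** Thirteen weeks separate the week-39 and week-52 clinic weights, and weight regain is one of the trial's own motivating problems. If a participant regains after week 39 and does not attend at week 52, the mixed model predicts the missing weight from that person's earlier clinic weights and the pattern among attenders. The regain itself is not in the data the model sees, although it may be in the class or home record. The MAR assumption therefore rests on less information than the trial holds.

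BOCF is a separate problem. It assigns zero change whether or not a recent weight was observed. Where missingness is similar in both arms, it pulls the arm difference toward zero. For a superiority test that is conservative. For the non-inferiority fallback it works the other way, so BOCF is a poor robustness check on that conclusion.

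**Working it through.** **Inputs** (Sample size {14}): SD of weight loss 5.6 kg; 75 per arm; attrition up to 20%, leaving 60 per arm; difference 3 kg; margin 2.26 kg; two-sided 5%.

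**1. The plan's own figures.** With a noncentral t, power for 3 kg is 90.3% at 75 per arm (stated 90%) and 82.9% at 60 per arm (stated 82%). Non-inferiority power at 75 per arm, no true difference, one-sided 5%, is 79.3% (stated 79%). All three reproduce. This point exposes no numerical error.

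**2. Shrinkage under BOCF.** Let m be the share missing in each arm, and assume missing participants have the same mean true change as observed ones. The expected BOCF difference is (1 − m) × true difference. With m = 0.20:

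- 3 kg becomes 0.8 × 3 = 2.4 kg.
- A true deficit at the margin becomes 0.8 × 2.26 = 1.81 kg, which is 0.45 kg inside the margin.

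If the arms differ in missingness, the expected difference is (1 − m_IMF) × change_IMF − (1 − m_DCR) × change_DCR, and the distortion can go either way.

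**3. Late regain not seen by the model.** Suppose missing participants have regained r kg more than the mixed model predicts. With 20% missing, the arm mean is wrong by 0.2 × r, and the arm difference by 0.2 × (r_IMF − r_DCR). Each kilogram by which unseen regain differs between arms moves the estimate by 0.2 kg. The article gives no value for r.

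**4. Precision at stake.** SE = 5.6 × √(2/n), measured against the completers' analysis. The share recovered is an assumption, and recovered weights are treated as precise as clinic weights, so these are upper limits on the gain.

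| Share of missing week-52 weights recovered | n per arm | SE (kg) | Power for 3 kg |
|---|---|---|---|
| none | 60 | 1.02 | 82.9% |
| half | 67.5 | 0.96 | 87.1% |
| all | 75 | 0.91 | 90.3% |

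The mixed model already uses weeks 13, 26 and 39, so the gain over the primary analysis is smaller than the table shows.

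**The case against.** The strongest reply is that this is analysis-plan detail. The SAP is not shown, the list of sensitivity analyses is worded as open, and the variables entering the imputation are not specified, so nothing excludes home or class weights. That stands as a reason for calling this an improvement and not an error. It does not rescue BOCF, which the article names explicitly.

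Other points also stand:

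- BOCF is only one of three sensitivity analyses; the primary method never substitutes baseline.
- Missed appointments are rescheduled, and post-allocation measures have a window of ±2 weeks, so a missed visit need not become a missing weight.
- Home and class weights lack the gown, the fasting and the fed-day condition. People who leave the trial may also stop weighing.
- Trial status reports a COVID-19 research shutdown but does not say that any week-52 weight was lost.

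A reader might infer two stronger claims. The first is that home weights exist for every participant. The article says only that scales are issued; the data depend on use. The second is that the IMF-only fed-day rule biases the comparison and cannot be checked. The rule is a deliberate standardisation, and no document gives the size of a fed–fast weight difference. Any upward shift in IMF weight would work against IMF on both superiority and non-inferiority. Dated home weights and the 7-day diet records allow a check, although none is described.

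**Conclusion.** The point holds as an inexpensive improvement to the sensitivity analyses. Clinic weight should remain primary. The stated missing-data methods ignore weights that may have been observed in the 13 weeks before the primary time point, and BOCF replaces a missing clinic weight with baseline even where such a weight exists.

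The BOCF shrinkage is 20% of the difference (3 to 2.4 kg; 2.26 to 1.81 kg), assuming equal 20% missingness and similar true change in missing and observed participants. The precision gain is modest: at most 1.02 to 0.91 kg against completers, and less against the mixed model. The main benefit is a more credible MAR assumption and a sensitivity analysis that does not lean toward non-inferiority. How much is recovered depends on how many non-attenders kept weighing or attending class, which the article does not tell us.

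**What to change.** 1. Name the latest class weights, and home-scale means near each due date, as auxiliary variables in the multiple imputation.
2. Add one named sensitivity analysis in which a missing week-52 clinic weight is replaced by a home or class weight taken near week 52. Correct it for each participant's offset using earlier paired weights. Rank this analysis ahead of BOCF.
3. If the fed-day rule is to be examined, do so descriptively: compare IMF home weights after fed and after fast days around week 52, without correcting them to the fed-day clinic weight. Such a correction would absorb the effect being looked for. A between-arm comparison of 7-day home means would be weak, because no pre-intervention home weight is described.
4. Reconcile the class-weight schedule. Group-based behavioral support has classes every two weeks from week 14, whereas the Table 3 footnote says "Weight will also be measured weekly during weeks 0–26 and every other week during weeks 27–52". Weeks 39 to 52 are unaffected.

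The cost is analysis wording and data processing; no new measurement is needed. The wording should be fixed before outcome data are analysed. Because home and class weights are less standardised and may be sparse among dropouts, these analyses stay supportive.

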#### Resting energy expenditure (REE)

At baseline and weeks 26 and 52, REE will be measured using indirect calorimetry (Parvo Medics TrueOne 2400, Salt Lake City, UT) in the AM in a thermoneutral (68–74 °F) quiet room after a 12-h overnight fast and 24-h abstention from exercise. After the participant has quietly rested for 30 min, a transparent plastic hood connected to the cart will be placed over the participant’s head. For the duration of the test, the participant will be asked to remain motionless and awake. Prior to each measurement, the pneumotach flowmeter will be calibrated using a 3-L calibration syringe (Hans Rudolph Inc., Shawnee, KS, USA), and gas analyzers will be calibrated using standardized gas mixtures. REE will be measured for 20 min and the average of the last 15 min of the measurement will be used to calculate REE using the Weir equation [46].

#### Free-living total daily energy expenditure (TDEE) and energy intake (EI)

TDEE will be measured using the DLW method at baseline and at weeks 26 and 52. Participants will arrive in the AM after a 12-h fast. A baseline urine sample will be collected prior to administration of the oral dose of DLW containing H_2_^18^O (10% atom percent excess, APE) and ^2^H_2_O (99.8% APE) mixed in a ratio of 15:1. Participants will consume a dose based on body weight and an estimation of total body water. Delivered doses will range from 0.85 to 1.10 g/kg of body weight for females and 0.95 to 1.15 g/kg of body weight for males. The dosing cup will be rinsed twice with 30 mL of water and the rinsing dose consumed. The exact time of dosing will be recorded. Urine will be collected after a 4-h and 5-h post-dose equilibrium period and then again on day 8 at the same time points. Sample aliquots (4 mL) will be frozen at −80°C until analysis. Frozen urine samples will be thawed and prepared by centrifugation and analyzed for ^18^O and ^2^H_2_ enrichment by Off-Axis Integrated Cavity Output Spectroscopy (OA-ICOS, Los Gatos Research Inc, Mountain View CA), as previously described [47]. TDEE will be determined using the two-point method according to Speakman et al. [48]; PAEE will be calculated as TDEE (0.9) − REE and PA level (PAL) as TDEE/REE.

EI will be calculated using the intake-balance method. Change in body composition (determined by DXA scan) will be used to calculate change in energy stores (ΔES) using 9.3 and 1.1 kcal/g as the energy coefficients of fat mass and fat free mass respectively [49]. EI will be calculated as TDEE + ΔES/Δtime [50]. However, because DLW cannot quantify macronutrient intake or provide information on patterns of EI on fed and fast days, 7-day diet records will also be collected at baseline and weeks 13, 26, 52, and 78. Diet records will be analyzed by Colorado Clinical and Translational Sciences Institute Nutrition Core personnel blinded to study group assignment using Nutrition Data System for Research software (University of Minnesota).

#### Patterns of PA and sedentary behavior

The activPAL^TM^ micro (activPAL4, PALTechnologies, Glasgow, Scotland) will be used to estimate time spent in moderate-to-vigorous PA (MVPA), light activity, and sedentary behavior over a 7-day period at baseline and weeks 13, 26, 52, and 78. The activPAL4 micro is a small (23.5 × 43 × 5 mm) and light (9.5 g) device that uses accelerometer-derived information about thigh position to estimate time spent in different body positions (i.e., sitting/lying, standing, and stepping). The device is attached to the anterior thigh and is waterproofed by wrapping in a nitrile sleeve. Thus, it can be worn during bathing and overnight, allowing for 24-h measurement of wake and sleep behavior. Raw activPAL.datx files will be processed using PALBatch software using the CREA – 24-h wear protocol (allows for 4 hours of non-wear per day) and auto-correcting for inverted wear (PAL Technologies Ltd., 2019). The algorithm will be used to determine time spent engaging in sedentary behavior, light activity, and MVPA. Many studies have validated the activPAL for use in adults and report very high levels of accuracy (96.2%) for estimating time in activity intensity categories [51–55]. Participants will also be asked to record all exercise and sleep times (i.e., bedtime and waketime) during the 7-day wear period.

#### Self-reported dietary adherence, effort, and self-efficacy

Self-reported dietary adherence and ratings of effort to adhere to the prescribed study diets will be obtained on a monthly basis during weeks 1–52 using methodology described by Dansinger et al. [2]. Participants will be asked to rate on a 1–10 Likert scale: (1) how adherent they were to the prescribed study diet over the past week, (2) how hard was it to adhere to the prescribed study diet over the past week, and (3) how likely they feel they can adhere to the prescribed diet for the next month. Participants in the IMF group will be asked to report the number of fast days over the past week. During weeks 53–78, monthly dietary follow-up questionnaires will be administered to evaluate participant efforts to continue weight loss or weight maintenance after the 52-week intervention has ended.

#### Metabolic/hormonal evaluations

A 12-h fasting blood sample will be obtained for assessment of glucose, insulin, hemoglobin A1c, lipid panel, leptin, ghrelin, peptide YY, and highly sensitive C-reactive protein (hs-CRP) at baseline and weeks 26, 52, and 78. Circulating nutrients and hormonal regulators of fuel metabolism (glucose, insulin, triglycerides, free fatty acids, beta-hydroxybutyrate, and cortisol) will be measured at baseline after both a fed (i.e., 12-h fast) and fast day (i.e., 36-h test fast day with 500 kcal/day (women) or 600 kcal/day (men)) to assess if baseline metabolic response to fasting can serve as a predictor of weight loss. Labs will be analyzed by the UCHealth Clinical Laboratory (beta-hydroxybutyrate) or the Clinical Translational Research Institute (CTRC, all other labs). Insulin sensitivity (homeostasis model assessment of insulin resistance, HOMA-IR) will be calculated as ([insulin] × [fasting glucose × 0.055]/22.5).

#### Psychosocial, behavioral, and environmental predictors of response

To measure psychosocial, behavioral, and environmental constructs which may predict weight loss response, several validated questionnaires and computer-based tasks will be administered to participants. Selection of measures was informed by the recommendations of the NIH ADOPT Core Measures Project [24, 27, 28]. Questionnaires will be administered at baseline and at weeks 13, 26, 52, and 78 (see Table 4). Each month, participants will also be asked to report any changes in their home or work address, to capture changes in their built, social, and community food environments.

**Table 4 Tab4:** Psychosocial, behavioral, and environmental constructs by study week

		Timepoint (week)				
Questionnaire	Construct measured	0	13	26	52	78
**Psychosocial**						
PANAS [56, 57]	Positive and negative affect	x	x	x	x	x
Perceived Stress Scale (PSS) [58–60]	Perceived stress	x	x	x	x	x
PEMS Coping Subscale [61, 62]	Eating motives	x	x	x	x	x
Binge Eating Scale (BES) [63]	Binge eating	x	x	x	x	x
RED [64]	Reward-based eating drive	x	x	x	x	x
Three-Factor Eating Questionnaire (TFEQ R 18) [65]	Restrained eating, uncontrolled eating, emotional eating	x	x	x	x	x
BREQ-3 [66, 67]	Motivation for exercise	x	x	x	x	x
Grit [68]	Perseverance and passion	x				
TSRQ-Baseline [69]	Motivation to start treatment	x				
TSRQ-Follow-Up [69]	Motivation to continue treatment		x	x	x	x
Mini-IPIP [70]	Personality	x			x	
BARSE [71]	Exercise self-efficacy	x	x	x	x	x
WEL-SF [72]	Diet self-efficacy	x	x	x	x	x
POMS (40-item) [73]	Mood	x	x	x	x	x
RAND-36 [74, 75]	Health-related quality of life	x		x	x	x
Life Events Questionnaire (LEQ) [76, 77]	Stressful life events	x		x	x	x
Behavior-based Identity [78]	Identity	x	x	x	x	x
Role/Group-based Identity Congruence^a^ [79]	Identity congruence	x	x	x	x	x
Emotion Regulation [80]	Emotion regulation	x	x	x	x	x
Psychological Well-Being [81]	Well-being	x	x	x	x	x
Attributional Style [82]	Attribution of events	x	x	x	x	x
Implicit Theory [83]	Beliefs about weight	x	x	x	x	x
Intervention Preference Baseline [study specific]	Intervention preference	x				
Intervention Preference Follow-up [study specific]	Intervention preference		x	x	x	x
Life History Questionnaire [study specific]	Perceived social economic status, developmental history	x^b^				
Computerized task-based assessments	Executive function	x	x	x	x	x
Monetary 5-trial adjusting delay discounting task	Delay discounting	x	x	x	x	x
UPPS+P Questionnaire [84]	Impulsivity	x				
**Behavioral**						
EARLY eating away from home Q [85]	Frequency of eating away from home	x		x	x	x
EARLY SSB Consumption Q [85]	Consumption of sugar-sweetened beverages	x		x	x	x
BRFSS Alcohol Consumption [86]	Alcohol consumption	x		x	x	x
GPAQ, with show cards [87, 88]	Self-reported physical activity	x	x	x	x	x
Munich Chronotype Q (MCTQ) [89]	Sleep	x	x	x	x	x
Marijuana Use (DFAQ-CU) [90]	Marijuana use	x				
BRFSS Marijuana Use [91]	Marijuana use			x	x	x
12-Month Study Questionnaire [study specific]	End of intervention questionnaire				x	
18-Month Study Questionnaire [study specific]	18-month follow-up questionnaire					x
